### Ethical Considerations

The study will be submitted to the Imperial College Research Ethics Committee at Imperial College London, London, United Kingdom. All participants will be provided with an information sheet detailing the aim and rationale for the research; inclusion and exclusion criteria; what will happen if they agree to take part; any risks of taking part in the study; clarification of the process for ensuring anonymity and confidentiality, including any limits to confidentiality; what information will be held about them and who will have access to it; possible benefits; and plans for project report. All participants will then be required to sign the informed consent form before participating in the study. Additionally, all participants’ identifiable data will first be anonymized. The identifiable and anonymized data will be stored in separate secure cloud-based databases (Azure PostgreSQL server) before being transferred to Research Data Store. Finally, each participant will be compensated £25 (US $31.15) per 2 weeks for their participation.

## Results

The planning and development of this study started in August 2022. We have since developed the chatbot MotivSleep. The chatbot’s design is being evaluated by carers, health care professionals, and occupational therapists and will be updated after their evaluation. The first cohort of participation recruitment will start in May 2023, the second cohort will begin in June 2023, and the third cohort will start in August 2023. The anticipated study completion date is December 2023.

In this study, we aim to test three hypotheses as follows:

First, we hypothesize that participants will perceive our chatbot as intelligent and trustworthy and are satisfied with our proposed MotivSleep.We also hypothesize that our proposed chatbot MotivSleep can improve participants’ subjective sleep assessment over their usage of the chatbot based on collected using ESS, ISI, PSQI, and SQS questionnaires and their objective sleep quality based on the Withing sleep analyzer.Finally, we hypothesize that participants’ objective sleep assessment will improve, measured by the Withings sleep analyzer.

## Discussion

### Principal Findings

Sleep disturbances are commonly observed among older people, with and without neurodegenerative disorders, and among carers for people with neurodegenerative disorders. This study will provide critical evidence pertaining to the feasibility and acceptability of the proposed chatbot MotivSleep, hosted on WhatsApp, which aims to conduct automatic sleep interviews and provide personalized recommendations for better sleep that may improve their sleep. Specifically, we evaluate the participants’ perceived usability and feasibility of the chatbot, changes in participants’ subjective sleep assessment before, during, and after the study, and changes in participants’ objective sleep assessment measured by the sleep tracking device Withings sleep analyzer.

This paper describes the protocol used in the MotivSleep study. To the best of our knowledge, no other studies have focused on developing an automated chatbot for older people with problematic sleep or conducting automated sleep interviews. The MotivSleep study aims to shed light on the feasibility of using a chatbot to conduct interviews for a prolonged period of time. Furthermore, the intervention and protocol were designed to be more accessible and simpler than frequent in-person assessment or intervention sessions. This allows future deployment to older adults with mobility issues or within hard-to-reach communities.

### Limitations

Our study requires participants to use 2 devices (a Withings sleep analyzer and a smartphone to access WhatsApp) and complete web-based questionnaires. As such, older people unfamiliar with or unwilling to use these devices might self-exclude. However, successful findings from this study could be leveraged to revise further to allow for more accessible options on the technological design for a broader audience and users. Additionally, excluding participants with diagnosed life-threatening illnesses and severe mental health problems is a limitation. However, for this preliminary study, such exclusion is warranted to ensure that participants are medically stable and not reporting severe clinical symptoms that would require a higher level of care, which a digital chatbot cannot help treat.

Furthermore, we acknowledge the small number of participants in this feasibility study. Thus, we do not expect to find significant differences with respect to gender or age. However, the proposed sample size aligns with previous research on the number of participants needed to assess usability and feasibility.

### Conclusions

To conclude, the MotivSleep study is innovative in using an automated chatbot to conduct sleep interviews for older people who wish to improve their sleep. Evidence of its feasibility and acceptability will facilitate a larger trial. Participants perceived changes and sleep tracking devices’ recorded changes will provide early evidence of its effectiveness. Moreover, the MotivSleep chatbot has the potential to be deployed by a large number of people due to its automated nature. This can offer older people access to supportive care that is more easily accessible and more affordable than face-to-face therapy with sleep experts.

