## Methods

### Overview

Once reviewed by the Imperial College Research Ethics Committee, we will recruit 30 healthy older adults (aged 65-90 years) in 3 cohorts through the UK DRI CRT community outreach group community outreach in West London. Participants will have access to the conversational agent through WhatsApp chat. We estimate that the average conversation will take less than 10 minutes. Each participant will also have access to the Withings sleep analyzer provided by the research group.

A poststudy questionnaire consisting of the GPIS, TPS, and NPS will be completed when the participant finishes the study. We analyze participants’ answers to assess the participants’ opinions on the proposed MotivSleep chatbot’s intelligence, trustfulness, and participants’ satisfaction with MotivSleep, to answer RQ1. Additionally, all participants will complete the ESS, ISI, modified PSQI, and SQS questionnaires before the start, fortnightly during the study, and at the end of the study. We analyze the answers to these questions to investigate RQ2.

The first cohort of 10 participants will use both the Withings sleep analyzer for 6 weeks (the first 2 weeks aims to establish baseline sleep assessments without the usage of MotivSleep) and the WhatsApp chatbot for 4 weeks, with WhatsApp message reminders to encourage WhatsApp chatbot engagement sent out fortnightly (ie, twice for the first cohort of 10 participants). The first batch of participants’ feedback and engagement measures will inform a new iteration of improvements.

The second cohort of 10 participants and the third cohort of 10 participants will use the WhatsApp chatbot for 8 weeks and 12 weeks and the Withings sleep analyzer for 10 weeks and 14 weeks, respectively. Participants will be reminded fortnightly (ie, 4 times for the second cohort participants and 6 times for the third cohort participants) to encourage participation with the WhatsApp chatbot when activated. After each cohort, participants’ technical feedback will be addressed by improving the software.

The feasibility study will have a single experiment condition that includes three types of features:

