### Recruitment

This study will be conducted in 3 batches. Participants in all 3 batches will be healthy older adults with no neurodegenerative disease. The participants will be recruited through the UK DRI CRT community outreach group in West London. The recruitment process follows the recommendations and requirements laid out in the UK National Institute for Health and Care Research Clinical Research Network policy, based on the inclusion and exclusion criteria. Specifically, Participants should be aged between 65 and 90 years, able to communicate fluently in English, experiencing sleep problems and wanting to improve their sleep, willing to install a Withings sleep analyzer and use the WhatsApp chatbot and have access to high-speed wireless internet connection at home, and able to provide informed consent. The exclusion criteria include the following: (1) people with unstable mental states, including severe depression, severe psychosis, agitation, and anxiety; (2) people with severe sensory impairment; (3) people who have active suicidal thoughts; (4) people who are receiving treatment for terminal illnesses.

Participants will be compensated for their time and inconvenience with £25 (US $31.15) per 2 weeks for participation, that is, for filling out the prestudy informed consent and questionnaires before, during, and after the study and engaging with the chatbot. The questionnaires will be provided on Qualtrics, separately to the chatbot, and sent to the participants as WhatsApp messages. Additionally, our team will teach the participants to complete the questionnaire using their smartphones before the study on an in-person visit when they sign the consent form. The subsequent questionnaires during the study will be sent to their mobile as WhatsApp messages.

A total of 30 individuals will be recruited in 3 cohorts. In total, we aim to include 18% of individuals who self-identify as members of a minority ethnic group to ensure alignment with the UK population [38] and avoid exclusion. Only approved phone numbers (of people who have consented to the study) can interact with the chatbot.

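### A single-arm before-after change in people enrolled for current sleep problems is presented as evidence that the chatbot works, and the Limitations do not mention the missing control or regression to the mean

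*Protocol article*

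**What the plan says.** **Design and entry.** Methods, Overview: "The feasibility study will have a single experiment condition that includes three types of features". Every participant receives the sensor, the chatbot and the reminders. The same section says "we will recruit 30 healthy older adults (aged 65-90 years) in 3 cohorts". Under Recruitment, participants must be "experiencing sleep problems and wanting to improve their sleep". No cut-off on any sleep scale is given.

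**Timing.** Cohort 1 uses the sleep analyzer for 6 weeks and the chatbot for 4. The first 2 weeks are a chatbot-free baseline. Cohorts 2 and 3 have 10 against 8 weeks and 14 against 12, which implies the same run-in. The four sleep questionnaires are completed "before the start, fortnightly during the study, and at the end of the study". The run-in is called a baseline only in connection with the sensor.

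**Claims.** RQ2 and RQ3 ask whether the chatbot can help improve subjective and objective sleep. The second hypothesis, in Results, is that "our proposed chatbot MotivSleep can improve participants’ subjective sleep assessment over their usage of the chatbot". The Conclusions add: "Participants perceived changes and sleep tracking devices’ recorded changes will provide early evidence of its effectiveness".

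**Limitations.** These cover self-exclusion by people unused to the devices, the excluded illnesses, and the small numbers. On size, the article says that "the proposed sample size aligns with previous research on the number of participants needed to assess usability and feasibility". The missing comparator, regression to the mean and time effects are not mentioned.

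**The concern.** A before-after change in one group is the sum of any chatbot effect and everything else that moves scores over the same weeks. Entry on a current complaint gives the second part a direction: people join when their sleep is worse than usual for them, and on average drift back. Being monitored, the in-person visit, payment, reminders and a May to December calendar also run alongside the chatbot and cannot be separated from it.

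The design is reasonable for feasibility. The difficulty is that the article goes further and assigns the change to the chatbot. A reader of the results could take a favourable change on one or more of the four subjective scales as showing that the chatbot improves sleep, when this design cannot show it.

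**Working it through.** **What can be reproduced.** The only sample-size figure is 30, which is 3 × 10. No error rate, power, effect size, SD or correlation is stated, so 30 cannot be derived from a formula.

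**Assumptions.** True chatbot effect zero; n = 30; two-sided 5% paired t-test, counting only significant improvement (nominal 2.5%); correlation *r* between baseline and follow-up scores; scores in population SD units. The article gives neither the test nor *r*, so ranges are shown.

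**Step 1, closed form.** If participants enter on average *d* SD worse than their population:

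- expected spontaneous improvement = (1 − *r*) × *d*
- SD of the change = √(2(1 − *r*))
- for *r* = 0.7 and *d* = 1: 0.30 / 0.775 = 0.387, and the noncentral t with 29 degrees of freedom gives 54%

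| *d* | *r* = 0.6 | *r* = 0.7 | *r* = 0.8 |
|---|---|---|---|
| 1 SD | 66% | 54% | 39% |
| 0.5 SD | 22% | 18% | 13% |

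**Step 2, selection tied to a figure in the article.** The Introduction says that 40% to 70% of older people report sleep difficulties. If the worst-scoring fraction *f* enters, *d* = φ(c)/*f* with c = z(1 − *f*). This gives 0.97 SD at *f* = 40% and 0.50 SD at *f* = 70%, so *d* = 1 in Step 1 is about the most selective end. Simulation with 20,000 replicates gives these chances of a significant improvement:

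| *f* | Correlation of entry selection with baseline score | *r* = 0.5 | 0.7 | 0.8 | 0.9 |
|---|---|---|---|---|---|
| 40% | 1.0 | 80% | 56% | 39% | 21% |
| 70% | 1.0 | 28% | 18% | 13% | 9% |
| 40% | 0.5 | 25% | 17% | 12% | 8% |
| 70% | 0.5 | 10% | 7% | 6% | 5% |

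Across the n = 30 scenarios with such selection, the mean change falls on the improved side in 62% to 99.8% of studies, against 50% without regression to the mean. If entry acts only through a stable trait, there is no regression and the rate is 2.6%.

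**Step 3, can the run-in change be subtracted?** With *r* = 0.7, *d* = 1 and no effect, expected scores are 1.0 at week 0, 0.7 at week 2 and 0.7 at the end.

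- Week 2 as reference: 0.7 − 0.7 = 0, so no bias in this model.
- Chatbot-period change minus run-in change: 0 − 0.30 = −0.30 SD, an apparent harm. The SD of this contrast is √(6(1 − *r*)) = 1.34, which is 1.34/0.775 = 1.7 times that of the simple change. A 5% test declares harm about 22% of the time (16% to 28% for *r* from 0.8 to 0.6).

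The run-in therefore helps as a reference point but not as a quantity to subtract.

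**The case against.** The strongest reply is that this is a self-described feasibility study, that its claim is hedged as early, and that before-after change is an ordinary thing for such a study to report. Several stronger readings also fail on the text:

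- **A larger trial launched on a spurious improvement.** A reader might infer this, but the Conclusions tie the larger trial to feasibility and acceptability, and no success criterion rests on sleep change.
- **Every sleep hypothesis credits the chatbot.** The third says only that objective sleep will improve on the sensor. The second does name the chatbot.
- **The first questionnaire precedes the run-in.** Teaching the questionnaire at the consent visit makes this the natural reading, but the text does not say whether the start means the sensor or the chatbot. Which visit serves as reference may also be settled in a fuller document.
- **A false-positive chance above one half.** That figure needs entry to select directly on the baseline score at about the most selective end of the range. Entry has no score threshold, so regression may be much weaker.
- **No safeguard exists.** For objective sleep, a sensor baseline over the two-week run-in is already planned. It reduces the problem there.

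These points limit the size and the consequence. They do not answer the central one. Calling evidence early qualifies its amount, not its attribution to the chatbot, and no analysis plan can supply a comparator that the design lacks.

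**Conclusion.** The point holds as a fault in the stated interpretation and should be fixed. The single condition, entry on current sleep problems, a causal second hypothesis and a conclusion about effectiveness together support an inference that the design cannot give, and the Limitations do not warn of it. The likely direction of the bias is favourable. Its size is not determined by the article: roughly 5% to 80% chance of a significant improvement per scale at n = 30 with no chatbot effect, depending on the assumed selection and retest correlation, and nominal if selection is on a stable trait only. The subjective scales are more exposed than the sensor measures. The documents do not support saying that a spurious result is probable, or that it would trigger the next trial.

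**What to change.** 1. Reword the second hypothesis, RQ2 and RQ3 as change during use of the chatbot.
2. In the Conclusions, replace the effectiveness claim with: *estimates of change and variability to plan a controlled trial*.
3. Add to the Limitations that there is no control group, and that regression to the mean and other time-related changes cannot be separated from a chatbot effect.
4. State when the first questionnaire is completed. For the questionnaires, take as reference the fortnightly assessment at the end of the two-week chatbot-free run-in, matching the sensor baseline already planned.
5. Report the run-in change separately and descriptively, with 95% confidence intervals, and do not subtract it from the chatbot-period change.

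**Cost.** Wording and analysis only. If the first questionnaire precedes the run-in, the week-2 assessment is already on the fortnightly schedule. If it is completed when the chatbot starts, it is itself the reference, and there is no run-in change on the questionnaires to report. The stated claim becomes less favourable. The week-2 reference reduces the bias but does not remove it: regression may not be complete by then, and the other uncontrolled influences remain.

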# Assessing a Sleep Interviewing Chatbot to Improve Subjective and Objective Sleep: Protocol for an Observational Feasibility Study

**DOI:** 10.2196/45752

**Published:** 2023-05-11

**Keywords:** automated chatbot, behavior analysis, conversational agents, older adults, sleep disorders, sleep interview

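### The single-condition before-after design cannot separate a chatbot effect from spontaneous change, yet the article promises early evidence of effectiveness and does not list this as a limitation

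*Protocol article*

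**What the plan says.** Discussion, Conclusions, states that participants' perceived changes and the device's "recorded changes will provide early evidence of its effectiveness". Under Research Questions, RQ2 and RQ3 ask whether MotivSleep can help improve subjective and device-measured sleep. The second hypothesis in Results says "our proposed chatbot MotivSleep can improve" subjective sleep, and adds objective sleep. The Abstract's Results carries the same hypothesis. The third hypothesis predicts better objective sleep but names no cause.

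On design, Methods, Overview, says "The feasibility study will have a single experiment condition that includes three types of features". The features are the sleep tracker with its analysis model, the chatbot, and WhatsApp messages that encourage its use. No comparison group is described. Recruitment requires participants to be "experiencing sleep problems and wanting to improve their sleep", with no cut-off on any scale. It also gives the size: "A total of 30 individuals will be recruited in 3 cohorts".

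Methods, Overview, includes two sensor weeks without the chatbot. This is explicit for the first cohort and implied for the others (10 against 8 weeks, 14 against 12). Limitations covers device access, exclusions and small numbers. It mentions neither the absent comparison nor spontaneous change.

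**The concern.** An effectiveness statement needs some account of what would have happened without the chatbot. People who enter a study because they are sleeping badly tend, as a group, to score better when measured again, treated or not. Fluctuating complaints, repeated self-rating and calendar trends between May and December 2023 can also move the scores, in directions the documents do not establish. The software is revised after each cohort, so version and calendar time move together. Reminders and tracking come with the chatbot, so even a genuine change would belong to the package.

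If the article stands as written, an improvement in the questionnaires or the sensor data can be presented as early evidence that the chatbot works, although the same data would be expected to some degree from an ineffective one. Two of the three research questions invite an answer that the design cannot give.

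**Working it through.** **1. The plan's own figures.** 10 + 10 + 10 = 30 participants. Sensor weeks are 4 + 2 = 6, 8 + 2 = 10 and 12 + 2 = 14. All agree with the text. No alpha, power, effect size or SD is given, so 30 cannot be derived from a formula. Limitations says only that "the proposed sample size aligns with previous research on the number of participants needed to assess usability and feasibility".

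**2. Assumptions for the illustration (none is in the documents).** The chatbot has no effect. The entry questionnaire score is the baseline. Selection acts on that same score. There are 30 complete pairs and a two-sided 5% paired t-test. Test-retest correlation r is 0.6 to 0.8. Mean entry is k SD worse than the reference mean.

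**3. Formulas.** Expected spontaneous improvement = (1 − r) × k SD. SD of change = √(2(1 − r)). Noncentrality = √30 × improvement / SD of change. The chance of a significant improvement is the upper tail of the noncentral t with 29 df beyond 2.045.

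| k | r | Improvement (SD) | SD of change | Noncentrality | Probability |
|---|---|---|---|---|---|
| 0.5 | 0.8 | 0.10 | 0.632 | 0.87 | 0.13 |
| 0.5 | 0.7 | 0.15 | 0.775 | 1.06 | 0.18 |
| 0.5 | 0.6 | 0.20 | 0.894 | 1.22 | 0.22 |
| 1 | 0.8 | 0.20 | 0.632 | 1.73 | 0.39 |
| 1 | 0.7 | 0.30 | 0.775 | 2.12 | 0.54 |
| 1 | 0.6 | 0.40 | 0.894 | 2.45 | 0.66 |

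The nominal rate in the direction of improvement is 0.025.

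**4. Which k is plausible?** The Introduction says that 40% to 70% of older people report sleep difficulties. If enrolment took the worst-scoring fraction q, mean entry would be φ(c)/q SD worse, where c is the cut-off: 0.97 for q = 0.4, 0.80 for q = 0.5 and 0.50 for q = 0.7. So k = 0.5 matches one end of that range and k = 1 lies just beyond the other. Simulating selection of the worse half (20,000 runs) gives 0.27 at r = 0.8, 0.41 at r = 0.7 and 0.53 at r = 0.6.

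**5. Later pre-chatbot baseline.** If the baseline is a separate measurement after selection, the expected change is (r₁ − r₂) × φ(c)/q. Here r₁ and r₂ are the correlations of the selection score with the baseline and with follow-up. With r₁ = r₂ = 0.7 the change is 0 and the probability is about 0.025. With q = 0.4, r₁ = 0.9 and r₂ = 0.7 it is 0.2 × 0.97 = 0.19 SD and the probability is 0.27. Across the settings run (q 0.4 to 0.7), the range is 0 to 0.20 SD and 0.025 to 0.27. A later baseline reduces regression to the mean but does not always remove it.

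**6. Sensor outcomes.** Participants are not selected on sensor values, so steps 3 to 5 do not apply directly to RQ3. The argument there is qualitative: no concurrent comparison, and a package of components.

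**7. Would a control arm at this size help?** Splitting the 30 into 15 and 15 gives about 28% power for a 0.5 SD difference. It would not establish effectiveness.

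**The case against.** A single arm is an ordinary choice for a feasibility study, and the sample size is tied to usability and feasibility. The title describes an observational feasibility study, the Conclusions say early evidence, and other passages are hedged. The Analysis Plan speaks of insight into changes over time and states no significance test or success rule for RQ2 or RQ3. The two chatbot-free weeks give the sensor outcomes a real baseline. All of this stands. It limits the size of the point and leaves RQ1 untouched. It does not supply the missing caveat, and early evidence of effectiveness is still evidence about effect.

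Several stronger readings are tempting, and the documents do not support them:

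- A reader might infer that spontaneous improvement will be reported as a chatbot effect. The documents support only that the two could not be told apart. The paired t-test above is an assumption.
- A reader might infer that the sleep changes will justify and size the larger trial. The Conclusions rest that trial on feasibility and acceptability.
- A reader might take the 1 SD figures as the expected case. No entry cut-off is given. Selection on a general complaint, and not on the analysed score, would produce less regression.
- A reader might count season as a cause of improvement. Nothing shows which way a calendar trend would run.
- A reader might call the third hypothesis causal. As worded, it predicts improvement without saying what produces it.

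**Conclusion.** The point holds as an over-claim in wording, of moderate severity. The Conclusions, RQ2, RQ3 and the second hypothesis attribute change to the chatbot. A design with one condition, several components and entry conditional on poor sleep cannot support that attribution, and Limitations is silent on it. This conclusion rests on the text alone.

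The numerical range only illustrates how easily an ineffective chatbot could appear to help. It depends on the assumed correlation, entry severity, test and choice of baseline, it applies to one questionnaire, and it should not be quoted as the study's error rate.

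**What to change.** 1. **Conclusions:** replace the effectiveness statement. Say that the changes will describe within-person change during use and supply variability and completion figures for a controlled trial, and that they cannot show effectiveness.
2. **Research Questions, Results and the Abstract's Results:** restate RQ2, RQ3 and the sleep hypotheses as estimation of change from the pre-chatbot to the chatbot period, with 95% intervals, for the package of chatbot, reminders and tracking.
3. **Benchmark:** use the chatbot-free sensor fortnight as the RQ3 baseline, and report the change from week 1 to week 2 beside the change after the chatbot starts. Do the same for the questionnaires only if one set is completed before that fortnight and one at its end. Methods, Overview, does not settle whether the study starts with the sensor or with the chatbot, so the sponsor should confirm the timing.
4. **Limitations:** state that there is no comparison group and that change therefore cannot be attributed to the chatbot.

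The cost is a more modest claim and one extra table. No control arm is requested.
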